### Exploring awareness, barriers and facilitators to uptake COS by trialists

2.3

**
*2.3.1 Online survey*
**

**2.3.1.1 The process of online survey**

A survey will be sent to clinical trialists who have registered or completed a clinical trial that has overlapped scope between the trial and COS. We will identify the primary investigator’s name, email, and telephone number when we extract eligible clinical trials from the Chinese Clinical Trial Registry. We will send a Chinese translation of the COS deemed relevant to the trialists’ trials with questionnaire. When the primary investigators cannot be contacted via emails, the applicants for registration will be approached. We will examine trialists’ knowledge and awareness of COS. An online survey will be sent to clinical trialists, with one of three versions of the survey: 1) clinical trialists who report a full COS in their clinical trials; 2) clinical trialists who report only a few of outcomes in the COS; and 3) clinical trialists who do not report any outcome in the COS.

The survey will include both closed and open-ended questions. General information, such as gender, age, participants’ role (clinicians or researcher), specialty (traditional Chinese medicine, integrative medicine, or Western medicine), work experience, geographical area, professional qualification, and educational background will be collected. We will refer to the facilitators and barriers identified in previous research, including using of COS and clinical practice guidelines,
^
10
^
^,^
^
11
^ to develop open and closed questions to ask all participants. MK, PW, and RQ will discuss the questions in the questionnaires. The survey and other tools will be distributed into Chinese. RQ will translate tools into Chinese and the translation will then be sent to several researchers who have experience in COS research from a Chinese authors’ team and we will ask them to give comments. RQ, SL, ZC, and WW will discuss and determine the translation before distribution.

The structured questions in the survey are shown in extended data.

At the end of each survey, we will ask the trialists if they would like to attend a semi-structured interview.

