## Background

1.

A core outcome set (COS) is an agreed standardized set of outcomes that should be measured and reported, as a minimum, in all clinical trials in specific areas of health or health care.
^
1
^ The concept of COS was introduced in China in 2013.
^
2
^ Chinese researchers have registered more than 80 COS for research in the Core Outcome Measures in Effectiveness Trials (COMET) database by 2022.

A search of the COMET database shows that more than 500 completed COS studies have been published by 2021. The number of COS varies by disease category. The top five disease categories are cancer, rheumatology, neurology, heart and circulation, orthopaedics and trauma.
^
3
^ However, the number of candidates vary by disease category. In addition, there are more than one COS for some conditions, while no COS exists in some other important conditions. Whether there are gaps between COS research and the burden of disease in China remains unclear.

There are some benefits to using COS in clinical trials, which include improving the consistency of outcome reporting, increasing the relevance of outcomes measured to decision-makers, and helping to identify potential selective outcome reporting bias. However, previous research has shown that COS uptake is low in most research areas.
^
4
^
^,^
^
5
^ Research shows that clinical trialists’ awareness and understanding of COS may facilitate the use of COS.
^
6
^ However, Chinese clinical trialists’ awareness, understanding and using of COS are unknown.

The aims of this study are to examine: (1) whether the top 25 diseases with the highest burden in China have relevant COS; (2) the use of COS in clinical trials registered in the Chinese Clinical Trial Registry for these 25 diseases; and (3) views of these clinical trialists on the knowledge, perceptions, and use of COS in relation to choosing outcomes, as well as barriers and facilitators to uptake of COS.

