**2.3.2.1 The process of semi-structured interviews**

We will invite trialists who agree to be interviewed to attend an in-person or online interview, if saturation is reached, the interviews will be completed. The COS publication, translated into Chinese, will be sent to them before the interview. The topic guide is as follows:
1.How many years of experience do you have in the design, management, or analysis clinical trials?2.How many clinical trials did you participate in the design, management, or analysis?3.When you design a clinical trial, how did you choose outcomes?4.Do you know what is COS?5.Are you familiar with COS?6.Can you define COS?7.How comfortable you are with English?8.How did you become familiar with COS?9.If there is a relevant COS in your research area, do you want to use it? Why?10.Whether you know the COS that we sent you? Will you use it in your next trial?11.What kind of facilitators and barriers for you to use a COS in clinical trial?12.In your opinion, what should be done to improve the use of COS?

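### Trialists are sent the translated COS before interview items on knowledge and familiarity that are not tied to the time before contact, so prior awareness is liable to be overstated

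*Protocol article*

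**What the plan says.** The Background of the protocol article states that Chinese trialists' awareness, understanding and use of COS are not known. Aim 3 is to examine "views of these clinical trialists on the knowledge, perceptions, and use of COS in relation to choosing outcomes", together with barriers to and facilitators of uptake.

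For the online survey, section 2.3.1.1 says "We will send a Chinese translation of the COS deemed relevant" to each trialist's trial, together with the questionnaire. The same paragraph states the purpose: "We will examine trialists’ knowledge and awareness of COS". The items themselves are elsewhere: "The structured questions in the survey are shown in extended data". Interviewees are recruited from the survey: "At the end of each survey, we will ask the trialists if they would like to attend a semi-structured interview".

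For the interview, section 2.3.2.1 says: "The COS publication, translated into Chinese, will be sent to them before the interview". Items 4 and 5 of the topic guide ask whether the person knows what a COS is and is familiar with COS. Item 6 reads "Can you define COS". Item 10 asks whether they know the COS that the study sent. Sections 2.3.1.2 and 2.3.2.2 plan descriptive, thematic and content analyses, and neither mentions that the material was sent beforehand.

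**The concern.** A measure of what people already know should be taken before they are given the material, or should ask explicitly about the earlier time. In the interview the plan does neither: it sends the publication first and then asks about knowledge, familiarity and definition in the present tense. A correct definition could reflect prior knowledge or a reading of the paper the day before, and the answer alone cannot separate the two.

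This matters because the Background treats awareness as the unknown that aim 3 should fill, and as something that may help uptake. If it is overstated, the study may report that trialists know more about COS than they did before being contacted, and so understate the case for dissemination. The order cannot be repaired once fieldwork is done, because a respondent who has read the COS cannot give an unexposed answer.

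**Working it through.** **1. The plan's own figure.** Section 2.2.3 wants 20 responses per COS at 50% non-response: 20 / (1 − 0.5) = 40 registered trials. This reproduces and is unaffected, since the point concerns the order of measurement and not the number of respondents.

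**2. Order of exposure and measurement.**

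| Step | Material sent | What is asked | Tied to before contact? |
|---|---|---|---|
| Online survey (2.3.1.1) | Translated COS, with the questionnaire | Knowledge and awareness of COS | Unknown: items are in extended data not shown |
| Interview (2.3.2.1) | Translated COS publication, beforehand | Items 4 to 6: knows, is familiar with, can define COS | No |
| Interview (2.3.2.1) | As above | Item 10: knows the COS that was sent | No |

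Interviewees come from the survey respondents, so by plan each has been sent the COS twice before items 4 to 6 are put. In the interview, sending clearly precedes asking. In the survey the two arrive together, and the text does not fix which is read first.

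**3. Direction.** Let a be the share truly aware before contact, and c the share of the unaware who answer as aware because of the material. Assume that the material makes no aware person answer as unaware. Then

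observed awareness = a + (1 − a) × c, and bias = (1 − a) × c.

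The bias is never negative, is zero when c = 0 (or when everyone is already aware), and for a given c is largest when a is low.

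**4. Illustration only.** The protocol gives neither a nor c, so all values below are assumptions. Cells show observed awareness.

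| a | c = 0 | c = 10% | c = 25% | c = 50% |
|---|---|---|---|---|
| 10% | 10% | 19% | 32.5% | 55% |
| 30% | 30% | 37% | 47.5% | 65% |
| 50% | 50% | 55% | 62.5% | 75% |

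Example: 0.30 + 0.70 × 0.25 = 0.475. Among 20 respondents with a = 30%, 6 are truly aware, and 6 to 13 would be recorded as aware as c runs from 0 to 50%. The bias ranges from nothing to 45 percentage points (a = 10%, c = 50%), so the table shows the direction and does not estimate the size. It applies to a survey proportion. The interviews run to saturation with descriptive and content analysis, and no awareness proportion is specified for them.

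**The case against.** The best defence concerns the survey. Sending the COS with the questionnaire does not mean that it is read before the awareness items, and being sent a document is not the same as having read it. The questionnaire may already ask awareness first, or ask about the time when the trial was designed. This stands. A reader might infer that every awareness answer in the study is given after exposure and that no unexposed measurement is planned; the text shown does not establish that for the survey.

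A second defence is that some prior unawareness will come out anyway. Item 3 asks how outcomes were chosen, and item 8 asks how the person became familiar with COS. Both analyses look at why trialists did or did not use a COS. The trials were in the main registered in 2021 and 2022, while the study began in April 2023, so a later mailing cannot change why outcomes were chosen then, and a trialist can still say that they had not heard of the COS. This partly stands: a reader might infer that lack of awareness will be lost as a barrier, and that goes too far. But these items can only reveal contamination after the event; they do not prevent it, and they do not rescue the definition item. Item 10 may be meant to ask about prior knowledge, but its wording does not say so.

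Third, sending the COS has a good purpose: trialists cannot comment on using a particular set without seeing it. This stands for topics 9 to 12, and is why the publication need not be withheld until partway through the interview. The mapping of COS to disease burden and the registry comparison of outcomes do not rest on these answers and are untouched.

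**Conclusion.** The point holds firmly for the interview: as planned, the answers on knowing, being familiar with and defining COS are open-book, and are liable to overstate awareness before contact. For the survey it is conditional on the questionnaire in extended data, and falls away if that form asks awareness first or ties it to before contact.

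The direction is upward, on the assumption that the material does not make aware people deny awareness. The size cannot be estimated from the protocol. It would be tempting to attach a percentage to the overstatement, but any such figure would come wholly from assumed inputs, and zero is among the possible values.

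**What to change.** - **Online form.** Put the awareness and knowledge items first, on a page that cannot be revisited. Release the translated COS only after they are submitted, then ask the questions about the specific COS. If the existing questionnaire already works this way, say so in section 2.3.1.1.
- **Interviewees' prior awareness.** Take it from that survey block, answered before the COS is released.
- **Topic guide.** Reword items 4 to 6 and 10 to ask about the time *before this study contacted you*, or *when you designed the registered trial*.
- **Advance reading.** The publication may still be sent before the interview so that topics 9 to 12 can be discussed.

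The cost is a reordering of the form and a rewording of four interview items, before fieldwork. The small downside is that anchored items rely on recall.

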**2.3.1.2 Data analysis**

Closed questions will be analyzed using descriptive statistics. Ratings for the barriers and facilitators to uptake will be summarized in terms of the median, range, and interquartile range. For open questions, thematic analysis will be used. All free text will be extracted in to a word document which RQ will read multiple times to organize the text into some initial themes and the author team will review the data and its assignment to the themes identified. The reason why the trialists used or did not use COS will be analyzed by content analysis. New suggested potential barriers and facilitators will be mapped to different themes.

**
*2.3.2 Semi-structured interviews*
**

**2.3.2.1 The process of semi-structured interviews**

We will invite trialists who agree to be interviewed to attend an in-person or online interview, if saturation is reached, the interviews will be completed. The COS publication, translated into Chinese, will be sent to them before the interview. The topic guide is as follows:
1.How many years of experience do you have in the design, management, or analysis clinical trials?2.How many clinical trials did you participate in the design, management, or analysis?3.When you design a clinical trial, how did you choose outcomes?4.Do you know what is COS?5.Are you familiar with COS?6.Can you define COS?7.How comfortable you are with English?8.How did you become familiar with COS?9.If there is a relevant COS in your research area, do you want to use it? Why?10.Whether you know the COS that we sent you? Will you use it in your next trial?11.What kind of facilitators and barriers for you to use a COS in clinical trial?12.In your opinion, what should be done to improve the use of COS?

**2.3.2.2 Data analysis**

General characteristics of interviewees will be presented using descriptive methods. The trialist’s awareness of, and decisions to search for and use a COS will be described, and the reasons why trialists used or did not use COS will be analyzed by content analysis.

### Dissemination

2.4

The finding of this research will be disseminated through conferences, peer-reviewed publication, and social media.

## Discussion

3.

COS have been introduced in China for about 10 years. Chinese trialists’ knowledge and awareness of using COS are important to COS developers in China. This study will provide information on the proportion of trialists in China who registered clinical trials in the Chinese Clinical Trial Registry in the areas with the highest burden of disease, and how the outcomes they chose compare to existing COS.

COS are very important for reducing heterogeneity of outcome reporting, potential bias, and research waste when they are used in clinical trials. There are hundreds of COS published in the world. Chinese researchers are also developing COS in some health areas, whether there is a gap between COS and the burden of disease in China remains unclear. This research will provide evidence relevant to COS researchers and clinical trialists.

## Ethics and consent

The project has been approved by the Ethics Committee of Dongzhimen Hospital, Beijing University of Chinese Medicine (2023DZMEC-175-01). The ethical approval agreed to not getting written informed consent from the participants, because they are clinical trialists.

**Trial registration:** This research is registered in Core Outcome Measures in Effectiveness:
https://www.comet-initiative.org/Studies/Details/2563.

## Data Availability

No data are associated with this article. DANS-EASY; Questionnaire of trialists’ perceptions in COS.
https://doi.org/10.17026/dans-ze4-tby3.
^
12
^ This project contains the following extended data:
•Questionnaire of trialists’ perceptions in COS(1).pdf. (English version of survey). Questionnaire of trialists’ perceptions in COS(1).pdf. (English version of survey). Data are available under the terms of the
Creative Commons Attribution 4.0 International license (CC-BY 4.0).
